**Methods:**

Adults aged 16 years or older undergoing valve or combined coronary artery bypass graft and valve surgery at one of three UK cardiac centers (Bristol, Hull, or Leicester) are randomly allocated in a 1:1 ratio to either a standard algorithm for optimizing tissue oxygenation during CPB that includes a fixed transfusion threshold, or a patient-specific algorithm that incorporates cerebral NIRS monitoring and a restrictive red blood cell transfusion threshold. Allocation concealment, Internet-based randomization stratified by operation type and recruiting center, and blinding of patients, ICU and ward care staff, and outcome assessors reduce the risk of bias. The primary outcomes are cognitive function 3 months after surgery and infectious complications during the first 3 months after surgery. Secondary outcomes include measures of inflammation, organ injury, and volumes of blood transfused. The cost effectiveness of the NIRS-based algorithm is described in terms of a cost-effectiveness acceptability curve. The trial tests the superiority of the patient-specific algorithm versus standard care. A sample size of 200 patients was chosen to detect a small to moderate target difference with 80% power and 5% significance (two tailed).

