### Primary Outcome

The patient-specific algorithm is designed to both prevent regional (cerebral) hypoxia and reduce the likelihood of a patient having an unnecessary RBC transfusion, compared to the generic algorithm. The primary outcome, cognitive function measured at 3 months after surgery, was chosen to measure the hypothesized benefits of preventing regional (cerebral) tissue hypoxia.

Cognitive function is assessed by a qualified examiner blinded to treatment allocation preoperatively, between 4 and 7 days postoperatively, and again at 3 months. The recommended tests [39] are performed in a fixed order (Textbox 3). In addition, to help interpret the cognitive function data, assessments related to the cognitive testing are carried out for all participants (Textbox 4).

Cognitive domain tests and order.Attention (first trial of the Rey Auditory Verbal Learning Test [RAVLT], and sustained and divided attention; Trail-Making Test parts A and B [40,41])Verbal memory (RAVLT [40,42])Visuospatial (block design from the Wechsler Adult Intelligence Scale-Revised (WAIS-R) test [43])Psychomotor speed (digit symbol test from the Wechsler Adult Intelligence Scale-Revised (WAIS-R) test [43])Executive function/verbal fluency (Controlled Oral Word Association Test [COWAT] [44])Motor coordination (Grooved Pegboard Test, dominant and nondominant hand [40])

Assessments related to the cognitive testing.The Wechsler Test of Adult Reading provides a preoperative measure of intellectual ability [45].Documentation of medications known to interfere with neuropsychological functions (including hypnotics, sedatives, neuroleptics, anxiolytics, antidepressants, and β-blockers) preoperatively, 4-7 days postoperatively, and 3 months postoperatively.Assessment of patient’s current mental health using the General Health Questionnaire (GHQ-30) and Hospital Anxiety and Depression Scale (HAD) [46] preoperatively, 4-7 days postoperatively, and 3 months postoperatively, to take into account the potential interaction between postoperative cognition and mood.

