### Sample Size

The cognitive outcomes are continuously scaled so target differences can be specified as “standardized differences” (0.2 is small; 0.5 is moderate; and 0.8 is large) [52]. In order to detect a small to moderate target difference with 80% power and 5% significance (two tailed), 200 patients (100 per group) are recruited. Specifically, this sample size allows the trial to detect standardized differences between groups of 0.33 (0.36 at 2.5% significance) in cognitive function (adjusting for baseline) and 0.46 in cost, while allowing for up to 12% dropout across the trial. Correlations between measures are assumed to be 0.5 between baseline and postintervention measures and 0.7 between repeated postintervention measures.

This sample size also allows a standardized difference of 0.3 to be detected for biochemical markers (adjusting for baseline and using 4 repeated measures). With respect to CICU and hospital discharge, the sample size allows a hazard ratio of at least 1.65 to be detected.

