### Statistical Analysis

The primary and other continuous outcomes are analyzed by regression modeling, transforming logarithmically if required, and jointly modeling baseline values where available using mixed models for repeated measures. Serial CPB oxygen delivery and utilization are compared between the 2 groups to determine whether this is improved using NIRS. Time to CICU and hospital discharge is analyzed by Cox regression.

The findings are reported as effect sizes with 95% confidence intervals. Frequencies of complications, which are too infrequent for the trial to be able to detect differences between groups, are tabulated descriptively in accordance with guidelines for reporting RCTs [53]. Analyses are based on intention-to-treat and are adjusted for center and surgery (valve or CABG and valve). For the study to conclude that the patient-specific algorithm is superior to the generic algorithm evidence of superior cognitive function for at least one domain at the 2.5% level is required (the significance level chosen to reduce the likelihood of a type 1 error, but not to be as conservative as a Bonferroni correction).

Health economic analysis are undertaken by the Health Economics Research Centre, University of Oxford. Analyses are designed and conducted to estimate the costs and likely cost of the alternative approaches identified in this protocol. These analyses help to determine whether there are likely to be improvements in patient health outcomes (such as morbidity through complications) associated with the proposed new algorithm, and whether better use can be made of scarce National Health Service (NHS) resources.

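### The primary outcome is cognition at 3 months, but the power figures are those of the average of the 4-7 day and 3-month visits, and the superiority rule does not say which contrast decides

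*Protocol article*

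**What the plan says.** The Primary Outcome section fixes the time point: "The primary outcome, cognitive function measured at 3 months after surgery, was chosen to measure the hypothesized benefits". The Methods paragraph of the Abstract agrees: "The primary outcomes are cognitive function 3 months after surgery". Cognition is tested "preoperatively, between 4 and 7 days postoperatively, and again at 3 months", so there are two assessments after surgery.

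Under Statistical Analysis, the primary and other continuous outcomes are analyzed by regression, "jointly modeling baseline values where available using mixed models for repeated measures". The conclusion rule in the same section is that "evidence of superior cognitive function for at least one domain at the 2.5% level is required". Neither sentence names the treatment contrast to be taken from the model.

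Under Sample Size, "with 80% power and 5% significance (two tailed), 200 patients (100 per group) are recruited". The detectable standardized difference in cognition, adjusted for baseline, is given as 0.33 (0.36 at 2.5%) with up to 12% dropout. The assumed correlations are 0.5 between baseline and later measures and "0.7 between repeated postintervention measures".

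**The concern.** A repeated-measures model with two postoperative visits can give a treatment difference at 4-7 days, one at 3 months, and one averaged over both. These answer different questions. At 4-7 days patients are still recovering from surgery and anesthesia, and a difference seen then may be gone by 3 months.

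The outcome definition points to 3 months. The 0.7 correlation between repeated postoperative measures has a role only when more than one of them enters the comparison, so the sample-size inputs point to an average. The sentence that decides the trial chooses neither. Two things are therefore at stake: whether the printed 80% power belongs to the stated primary outcome, and whether a short-lived early effect could support the superiority conclusion.

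**Working it through.** **Inputs from the article.** 100 per group less 12% gives n = 88 per group. The baseline correlation is 0.5 and the correlation between postoperative measures is 0.7. Power is 80% and the level is 5% or 2.5%, two-sided. Textbox 3 lists six cognitive domains.

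**Formulas, in SD units.** Baseline-adjusted variance of the mean of k postoperative measures: v = (1 + (k − 1) × 0.7)/k − 0.5². Standard error: SE = √(2v/88). Detectable difference: (z for the level + z for power) × SE. The multipliers are 1.960 + 0.842 = 2.802 at 5% and 2.241 + 0.842 = 3.083 at 2.5%.

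**Step 1: reproduce the stated figures.**

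| Contrast | v | SE | Detectable at 5% | Detectable at 2.5% |
|---|---|---|---|---|
| Average of both visits (k = 2) | 1.7/2 − 0.25 = 0.60 | 0.117 | 0.327 | 0.360 |
| 3 months alone (k = 1) | 1 − 0.25 = 0.75 | 0.131 | 0.366 | 0.403 |
| Stated | – | – | 0.33 | 0.36 |

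Only the averaged row matches. Other constructions also miss the stated pair:

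- 3 months alone with no dropout (100 per group): 0.343 and 0.378.
- Average of both visits with no dropout: 0.307 and 0.338.
- A change score, or no baseline adjustment, at a single visit with 88 per group: 0.422 and 0.465.

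The biomarker figure is a cross-check. With four repeated measures, v = (1 + 3 × 0.7)/4 − 0.25 = 0.525, and the detectable difference at 5% is 2.802 × √(1.05/88) = 0.306, against the stated 0.3. The same averaging formula accounts for it.

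**Step 2: power at 3 months for the stated differences, one domain.**

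- 0.33 at 5%: 0.33/0.1306 − 1.960 = 0.568, so power is 71.5%.
- 0.36 at 2.5%: 0.36/0.1306 − 2.241 = 0.516, so power is 69.7%.

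For 80% power at these differences, 109 and 111 per group are needed after dropout. Dividing by 0.88 and rounding up gives 124 and 127, or 248 and 254 in total, in place of 200.

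**Step 3: an effect at 4-7 days only.** The article gives no size for such an effect, so 0.4 SD early and zero at 3 months is an assumption. In a single affected domain the average is 0.2, and 0.2/0.1168 − 2.241 = −0.53. A favorable result at the two-sided 2.5% level then has probability about 30% with the averaged contrast and 1.25% with the 3-month contrast. The single-domain result depends on the assumed size: with the averaged contrast it is 24% for an early effect of 0.36 and 80% for 0.72.

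For six domains the correlation between domains is also an assumption, taken from 0.3 to 0.7. Simulated chance that at least one domain is favorable at 2.5%:

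| Early-only effect of 0.4 SD | Averaged contrast | 3-month contrast |
|---|---|---|
| In one domain | 30-32% | about 4-6% |
| In all six domains | 57-75% | about 4-6% |

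The 3-month column is the chance of a false favorable result across six domains, since nothing is true at that visit.

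**The case against.** The strongest reply is that the time point is fixed where it should be. The Abstract and the Primary Outcome section both say 3 months, Statistical Analysis opens by referring to the primary outcome, and the rule is naturally read as applying to it. The mixed model is described as a way to include baseline values, and such a model routinely gives a visit-specific contrast. The exact model terms can be left to an analysis plan that is not shown. All of this stands.

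A reader might go further and infer that the planned analysis averages the two visits, so that an early effect would win the trial. The article does not support that. Averaging can be shown for the power figures only. The 57-75% also needs three conditions together: an averaged deciding contrast, an early effect in all six domains that exceeds the trial's own 0.33-0.36 target, and no effect at all at 3 months.

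A reader might also infer a large rise in false-positive risk from a free choice among contrasts. The article grants no such choice. Only favorable results can meet a superiority rule, so the relevant rates are one-sided. At a between-domain correlation of 0.5 they are about 5.7% for 3 months alone, 7.9% if the average were also allowed, and 10.2% if the 4-7 day contrast were allowed too.

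The reply does not remove the conflict. If the rule means 3 months, the printed power belongs to a different contrast. An analysis plan can agree with the outcome definition or with the sample-size figures, but not with both.

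**Conclusion.** The point holds as an inconsistency within the article. The primary outcome is at 3 months, the stated detectable differences are those of a two-visit average, and the superiority rule does not say which contrast decides. On the natural 3-month reading, power per domain is about 71% for 0.33 at 5% and 70% for 0.36 at 2.5%. The chance of success in at least one of several domains is a separate and larger quantity. On the averaged reading, a transient early effect could meet the rule with the conditional probabilities above. They show what hangs on the choice and do not predict the result.

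The calculations assume equal variance at both visits, a normal approximation and 12% loss at both visits. If fewer patients miss the 4-7 day visit, the mixed model recovers a little precision at 3 months. Even with no loss at all the 3-month figure at 2.5% is 0.378, still above 0.36. Severity is moderate: the question of which test decides the trial is material, but it is easily settled.

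**What to change.** Under Statistical Analysis, make the rule apply to the treatment difference at the 3-month visit, estimated from a mixed model with a treatment-by-visit interaction. State that the 4-7 day and visit-averaged contrasts are secondary and cannot support the superiority conclusion.

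Under Sample Size, restate the detectable differences for that contrast as about 0.37 at 5% and 0.40 at 2.5%, with 200 patients, 80% power and 12% dropout. Changing the rule alone would leave the printed power attached to a contrast that is now secondary.

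The cost is a few sentences and no new data. The downside is a less favorable stated figure, because the 3-month contrast is less precise (SE 0.131 against 0.117 SD). The article describes the results as still to be published, so the deciding contrast could be put on record before they are reported.

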### Ethical Approval

The South West Research Ethics Committee approved the trial protocol on June 15, 2009.

### Adverse Events

Serious and other adverse events are recorded and reported in accordance with the International Conference for Harmonisation of Good Clinical Practice (ICH GCP) guidelines and the Sponsor’s (University Hospitals Bristol NHS Foundation Trust) Research Related Adverse Event Reporting Policy. Castle Hill and Glenfield Hospital will notify the coordinating center (Clinical Trials and Evaluation Unit, Bristol) of all serious adverse events. Data on adverse events are collected from the time of surgery for the duration of the participant’s postoperative hospital stay and for the 3-month follow-up period.

### Measures to Reduce the Risk of Bias

Concealed randomization prevents selection bias. To assess protocol compliance, interventions made as part of the patient-specific algorithm are logged. NIRS cerebral saturation monitoring is also conducted on patients allocated to both the generic and patient-specific groups to document whether the intervention resulted in significant separation of mean NIRS values. The NIRS values are carefully concealed from the theater team in the generic group. Surgical, anesthetic, and perfusion staff in the theater cannot be blinded to allocation but every effort is being made to ensure that patients, CICU, and other ward care staff and outcome assessors are blinded to minimize performance and detection bias. To further minimize detection bias, outcome measures are defined on the basis of objective criteria. Data are collected for all patients during surgery to characterize compliance with the randomly allocated transfusion protocol. Analysis is on the basis of intention-to-treat.

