### Randomization

Participants are randomized in blocks of varying size in a 1:1 ratio, stratified by center and planned surgery (valve only or combined CABG and valve). Allocations are generated by computer in advance of starting recruitment and are concealed using an Internet-based system. To maintain blinding, a member of the staff who is not involved in data collection, neurocognitive assessment, or providing health care randomizes participants shortly before surgery. The allocation is given to the responsible clinical perfusionist in a sealed envelope by the trial coordinator. If surgery is unexpectedly rescheduled, participants retain their study numbers and allocation. Eligible patients who consent to participate and who have an MMSE score of 24 or greater are randomly allocated to one of two different algorithms for optimizing tissue oxygenation during CPB (Textbox 2).

Algorithms for optimizing tissue oxygenation.“Generic algorithm” (including a standard transfusion threshold): Based on global measures of oxygen utilization and includes a predefined intraoperative hematocrit transfusion threshold of 23 (current standard practice, the existing protocol).“Patient-specific algorithm” (including a restrictive transfusion threshold): Patient-specific, goal-directed algorithm based on the monitoring and optimization of regional cerebral oxygen saturation, combined with a predefined restrictive intraoperative hematocrit transfusion threshold of 18.

For patients allocated to the patient-specific algorithm, optimization of cerebral oxygenation uses a protocol based on that suggested by Murkin and colleagues [8]. Target regional oxygen saturation values are specified as 70% or more of preinduction values and an absolute value of 50% or more. However, if the regional oxygen saturation remains at or above these target values, but the hematocrit falls to 18, then RBC transfusion is indicated (this represents a measure to increase patient safety and protect participants from possible risks associated with the experimental intervention). Several measures are taken to maintain these targets (Table 1).

**Table 1 table1:** Cerebral oxygenation optimization protocol to maintain cerebral oximetry readings within 70% of baseline and greater than 50%.

Measure	Description
Equipment check	Bypass pump, oximeter sensors, head and aortic cannula position
Cerebral perfusion pressure^a^ (CPP) <60 mmHg	Raise CPP > 60 mmHg by administering 0.5 mg metaraminol

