If no effect and CPP < 80 mmHg	Raise CPP > 80 mmHg by administering 0.5 mg metaraminol
Partial pressure of CO_2_ in arterial blood (PaCO_2_) < 35 mmHg	Raise PaCO_2_ to 40-45 and reduce gas flows
Inspired oxygen concentration (FiO_2_) < 0.6%	Raise FiO_2_
If no effect and FiO_2_ < 1.0	Raise FiO_2_ to 1.0
Decrease cerebral metabolic rate	Increase depth of anesthesia by increasing the propofol infusion rate
Increase pump flow to maximum tolerated by venous reservoir	
Target not met and critical hematocrit is 18-23	Transfuse 1 unit of RBC

^a^CPP=mean arterial pressure (MAP)-central venous pressure (CVP).

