#### Near-Infrared Spectroscopy Monitoring of Cerebral Oxygenation

Regional oxygen saturation of blood in the cerebral cortex is measured using the INVOS 5100 regional oximeter (Somanetics, Troy, MI, USA) [10]. NIRS readings are recorded for patients in both study arms for comparison. Bilateral NIRS sensors are attached to the patient’s forehead prior to preoxygenation and anesthetic induction to calculate baseline values. Cerebral oximetry is continuously measured and recorded for the duration of the operative procedure and discontinued once the patient has left the operating theater.

For patients randomized to the patient-specific algorithm (intervention group), the protocol for perioperative optimization of cerebral oxygenation/transfusion (described in Table 1) is performed. The list of interventions used to optimize cerebral oxygenation is logged. For patients randomized to the generic algorithm (control group), NIRS measurements are recorded for comparison but the clinical team is blinded to these readings in theater and optimization of tissue oxygenation is based on global measures of oxygen utilization only (ie, current standard procedure). For patients in both groups, on return to the cardiac intensive care unit (CICU), the clinical team caring for the patient is blinded to the allocation and the NIRS readings from the operative period.

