Secondary outcomes.Units of RBC and other blood components transfused during the operative period and postoperative hospital stay are recorded.Cerebral oxygenation during the operative period: NIRS readings are recorded for both groups for comparison. Monitoring starts before preoxygenation and anesthetic induction and continues until the patient leaves the theater.Oxygen delivery and utilization during CPB: serial measurements of oxygen delivery and utilization are collected from the clinical perfusion record.EuroQol EQ-5D-3L (a generic health related quality of life instrument that measures mobility, self-care, usual-care, pain/discomfort, and anxiety/depression): assessed at baseline and at 6 weeks and 3 months after surgery.Length of CICU or high dependency unit (HDU) stay.Length of postoperative hospital stay.Clinical outcomes defined as infectious complications (sepsis and wound infection), stroke (validated by CT scanning), ST elevation myocardial infarction accompanied by troponin >5 ng/mL, postoperative acute kidney injury (defined as AKIN criteria stage 1, 2, or 3 [47]), and respiratory complications (ie, reintubation, ventilation >48 hours, tracheostomy, or acute respiratory distress syndrome).Sepsis is defined when antibiotic treatment is required for suspected infection and the presence of systemic inflammatory response syndrome (SIRS) within 24 hours prior to start of antibiotic treatment. Sepsis occurring postdischarge only contributes if the event results in admission to hospital or death; wound infection is considered in the following scenario: ASEPSIS score >20, sternum, and if applicable, leg and arm. Wounds will be assessed at least once during a participant’s hospital stay. A questionnaire will be administered at 3 months to identify wound infections arising after discharge.For stroke diagnosis, blinded assessment of brain imaging (CT or MRI), in association with new onset focal or generalized neurological deficit (defined as deficit in motor, sensory, or co-ordination functions) will be performed.Cumulative resource use, cost, and cost effectiveness.All-cause mortality within 30 days of surgery.Biochemical markers of organ injury.

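### Mean NIRS, the only separation measure the protocol names, is an insensitive check on an algorithm built to keep saturation above a floor

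*Protocol article*

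**What the plan says.** All references are to the protocol article.

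- **Separation check.** Measures to Reduce the Risk of Bias gives the reason for monitoring NIRS in both arms: "to document whether the intervention resulted in significant separation of mean NIRS values". The meaning of significant is not developed further.
- **Target.** Randomization sets a floor: "Target regional oxygen saturation values are specified as 70% or more of preinduction values and an absolute value of 50% or more". Table 1 lists the steps and is captioned "Cerebral oxygenation optimization protocol to maintain cerebral oximetry readings within 70% of baseline and greater than 50"%. I take this to be the same target.
- **Red cells, patient-specific arm.** Below target, the last step of Table 1 applies when "Target not met and critical hematocrit is 18-23". On target, the rule is: "if the regional oxygen saturation remains at or above these target values, but the hematocrit falls to 18, then RBC transfusion is indicated".
- **Red cells, generic arm.** The algorithm "includes a predefined intraoperative hematocrit transfusion threshold of 23", without regard to NIRS.
- **Data.** "Cerebral oximetry is continuously measured and recorded for the duration of the operative procedure", in both arms.
- **Secondary outcome.** For cerebral oxygenation, "NIRS readings are recorded for both groups for comparison". No summary measure is named.

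**The concern.** The algorithm responds to low saturation, and its purpose is to prevent cerebral hypoxia. The Primary Outcome section says the cognitive endpoint was chosen to measure the benefit of preventing it. No step in Table 1 is aimed at raising readings that already meet the target. A mean over the whole operation gives most of its weight to those readings, so even a large reduction in desaturation may move it very little.

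The same arm also holds back red cells at hematocrit 18-23 while NIRS is on target, whereas the generic arm transfuses at 23. If lower hematocrit lowers NIRS, this pulls the mean the other way.

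What is at stake is interpretation. Suppose the cognitive result is null and mean NIRS does not separate. It would be natural to write that the algorithm did not change cerebral oxygenation, although time spent below the floor might have fallen sharply. A positive cognitive result could equally be left without its proper mechanism.

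**Working it through.** **1. The plan's own figure.** The article gives no effect size, SD or power for NIRS. Its detectable difference of 0.33 SD (0.36 at 2.5%) concerns cognition. It reproduces with 100 x 0.88 = 88 evaluable per arm and two post-surgery measures adjusted for baseline:

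- variance factor (1 + 0.7)/2 - 0.5^2 = 0.60
- sqrt(0.60) x (1.960 + 0.842) x sqrt(2/88) = 0.327
- at 2.5%: sqrt(0.60) x (2.241 + 0.842) x sqrt(2/88) = 0.360

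That figure is not in dispute. The NIRS inputs below are all assumptions.

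**2. Hand calculation.** If desaturation is fully prevented and nothing else changes, the mean shifts by proportion desaturating x fraction of time x depth. With 100 per arm, power is approximately Phi(d x sqrt(100/2) - 1.96), plus a small opposite tail. The assumed between-patient SD is 8 points, so 80% power needs 2.80 x sqrt(2/100) x 8 = 3.17 points (0.40 SD).

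| Case | Mean shift | In SD | Power on mean |
|---|---|---|---|
| 25% of controls, 15% of time, 5 points | 0.25 x 0.15 x 5 = 0.19 | 0.02 | 5% |
| Extreme: 50%, 30% of time, 10 points | 0.50 x 0.30 x 10 = 1.5 | 0.19 | 26% |

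Baseline adjustment helps the mean. In the extreme case:

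- baseline correlation 0.5: residual SD 8 x sqrt(1 - 0.25) = 6.93, d = 0.22, power about 33%
- baseline correlation 0.8: residual SD 8 x sqrt(1 - 0.64) = 4.8, d = 0.31, power about 60%

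For scale, a comparison of 30% v 10% ever desaturating has 95% power by the arcsine method: h = 0.516, and 0.516 x sqrt(50) - 1.96 = 1.69. This is a different scenario from the two rows above, so it is not a like-for-like contrast.

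**3. Like-for-like check by simulation.** Both measures were computed on the same simulated patients, with 100 per arm and 500 trials per scenario (simulation error at most about 2 percentage points). Assumptions:

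- baseline mean 65 or 70, SD 8
- mean intraoperative fall 4 or 8 points, between-patient SD 5, within-patient SD 3
- the algorithm corrects 80% of any shortfall below the higher of 70% of baseline and 50, with no carry-over

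The mean was baseline-adjusted. Depth is the shortfall averaged over the operation, that is, area below the floor divided by recording time; it was compared by Welch t-test.

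Without a hematocrit effect:

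| Baseline, fall | Controls ever below | Mean difference | Power on mean | Depth, control to intervention | Power on depth |
|---|---|---|---|---|---|
| 70, 4 | 13% | +0.18 | 6% | 0.22 to 0.05 | 25% |
| 70, 8 | 24% | +0.42 | 10% | 0.54 to 0.11 | 70% |
| 65, 4 | 27% | +0.57 | 12% | 0.67 to 0.13 | 80% |
| 65, 8 | 42% | +1.14 | 36% | 1.40 to 0.28 | 99.6% |

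Depth falls by about four fifths in every row.

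**4. Adding a hematocrit effect**, assumed in half of the patient-specific arm:

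- 2-point cost: mean difference -0.8 to +0.3; power on depth 14% to 97%.
- 4-point cost: mean difference -1.7 to -0.4, significantly negative in 9% to 64% of trials. Depth still falls by 64% to 72%, with power 9% to 94%.

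**The case against.** The strongest reply is that the sentence explains why both arms are monitored and is not an analysis rule. Statistical Analysis contains no mean-NIRS test, the secondary outcome fixes no summary, and a SAP not shown here could add desaturation measures. This is fair as far as it goes. The mean is nevertheless the one summary the article names, and the objection is to that choice, not to missing detail.

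A reader might infer more than the documents support, in four ways:

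- **That lack of mean separation would count as failed delivery.** The same section assesses compliance through the log of interventions, and deviations from the transfusion protocol are documented on the CRF. The log does not settle the matter, because it covers one arm and records actions, not the saturation achieved.
- **That the algorithm does nothing above the floor.** The introduction speaks of saturations approaching a threshold, transfusion at hematocrit 18 is triggered on target, and the effects of Table 1 steps may persist after recovery. Carry-over would raise the mean shift above the figures given here.
- **That the mean is expected to reverse.** This needs a hematocrit effect on NIRS that the document does not quantify. A lower mean would also be a true effect of the whole package, since the restrictive threshold is part of it.
- **That a burden measure is always adequate.** It is not: power on depth fell to 25% without a hematocrit effect, and to 9% with one, when only 13% of controls reached the floor.

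**Conclusion.** The point holds as a mismatch between the named summary and the goal of the algorithm. The direction comes from the document: steps triggered around a floor are judged by a mean made up largely of readings on target. The size does not come from the document. Without a hematocrit effect, power on the mean is roughly 5% to 36% over the assumed ranges, and up to about 60% in the extreme case with a baseline correlation of 0.8. Depth below the floor had more power than the mean in each of those simulated scenarios (25% to 99.6%).

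The consequence is limited. The superiority conclusion rests on cognitive function alone, and no decision depends on NIRS separation. What is exposed is the explanation offered for the cognitive result. This is worth correcting, but it does not threaten the primary comparison.

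**What to change.** In Measures to Reduce the Risk of Bias, and for cerebral oxygenation under Secondary Outcomes, state that separation between arms is judged mainly on time and area below each patient's own target, taken from the protocol as the higher of 70% of baseline and 50%. Give the proportion of patients ever below target as support. It should not lead, because a low reading is what triggers the steps, so brief excursions can still occur in the patient-specific arm. Report baseline-adjusted mean NIRS, with its confidence interval, as description.

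The cost is some extra analysis of traces already recorded continuously in both arms; no new data are needed. Follow-up ended in April 2014, so if the measure is set after data have been seen, it should be labelled as such.
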